## Introduction

Hepatitis C is a form of liver disease caused by the hepatitis C virus (HCV). An estimated 71 million people globally and 1 million people in Japan have chronic HCV infection. Chronic infection leads to liver cirrhosis and eventually to hepatocellular carcinoma (HCC) [1], and remains the primary cause of liver cirrhosis and cancer in Japan [2]. However, advances in such therapeutic agents as direct acting antivirals (DAAs), with sustained virological response (SVR) rates of over 95% [3, 4], have reached a stage where it is possible to eliminate HCV entirely.

The World Health Organization (WHO) has announced its commitment to eradicate HCV by the year 2030 via a series of therapeutic measures. However, assuming that high-income countries maintain their current levels of diagnosis and treatment, only 24% are on track to eliminate HCV by 2030, and 60% are off track by at least 20 years [5, 6]. Among developed nations, Japan appears to be on schedule to meet the WHO’s HCV elimination target and should maintain its current levels of HCV diagnosis and treatment. However, improved screening and management remain crucial to ensure the WHO’s goal is met. Specifically, chronic HCV infection is often undiagnosed because it remains largely asymptomatic until the progression to liver cirrhosis or HCC, which highlights the importance of screening and early detection.

In addition to preventing primary and secondary infections, three steps have been outlined to eradicate HCV: 1) Examination to identify HCV-positive individuals through HCV testing, 2) Consultation after encouraging HCV-positive individuals to see hepatologists at medical institutions, and 3) Treatment by eradicating HCV with appropriate DAA interventions. These policies are carried out based on the Basic Act on Hepatitis Measures in Japan. However, from the viewpoint of total HCV eradication, the current rates of HCV testing, medical institution consultations, and treatment may be insufficient; in fact, no region in Japan has successfully eradicated HCV.

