"Micro-elimination" is an approach that seeks to quickly and efficiently enable treatment and prevention by applying national-level eradication goals to specific populations, such as certain regions or people with certain demographics [7]. In order to eradicate HCV, it will be important to first perform HCV testing on everyone in a regional cohort (i.e., Examination), then increase the rate of secondary examinations by motivating people testing positive to seek medical advice (Consultation) and receive DAAs (Treatment). Achieving micro-elimination in this way is considered the first step towards eradicating HCV in Japan.

The rural town of Nagawa in the Chiisagata district of Nagano Prefecture (population: 5,903 as of September 1, 2020; mayor: [name]) has been pursuing an aggressive health check-up initiative since May of 1972 under the municipal government’s Children and Health Promotion Division. A system has been created that allows residents to undergo a so-called “Ningen Dock” general health check-up and a metabolic syndrome-specific check-up in alternating years, with certain examinations provided at no cost to the individual. The town’s only public medical institution is Yodakubo Hospital (https://www.yodakubo-hp.jp/), at which all extensive health check-ups are carried out. The metabolic syndrome-specific health check-ups are performed as part of mobile health screenings in every town district with the assistance of the hospital. In addition, many residents with chronic illnesses visit Yodakubo Hospital on a regular basis. Based on the above circumstances, Nagawa town is considered a suitable candidate for the “Nagawa Project” for HCV micro-elimination.

Developed in Japan, MAC-2 binding protein glycosylation isomer (M2BPGi) is a novel serum glycan marker whose secretion from hepatic stellate cells increases with hepatic fibrosis progression [8]. We have described the clinical usefulness of M2BPGi for diagnosing liver fibrosis in chronic liver disease and demonstrated its usefulness as a prognostic biomarker in liver disease and cancer [9–12]. Therefore, the inclusion of M2BPGi results may help in motivating otherwise asymptomatic HCV-positive patients to seek further medical consultation and commence DAA treatment.

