#### Trial design and follow-up

Participant registration for the study will run from June 1, 2021, to September 30, 2023. All participants will undergo HCV antibody II (HCVAb) testing (Sysmex Co., Kobe, Japan) and M2BPGi (Sysmex Co., Kobe, Japan) measurement with a HISCL-5000 (Sysmex Co., Kobe, Japan) system using stocked serum. An HCVAb test result ≥1.00 cutoff index (COI) is considered a positive result. M2BPGi readings of <1.00 COI, ≥1.00 COI and <3.00 COI, and ≥3.00 COI, are judged as negative, 1+, and 2+, respectively. Regarding linkage-to-care, if an HCV-positive patient has a high M2BPGi value, this will be used to explain that the risk of cirrhosis and HCC is high at present, and early consultation and treatment will be urged. On the other hand, if M2BPGi is low in an HCV-positive patient, clinicians will make the individual aware of the possibility of progression to cirrhosis and HCC with the onset of fibrosis, at which point M2BPGi will being to rise, and that treatment is crucial to prevent further M2BPGi increases. When the M2BPGi results are returned, an explanatory document with the above descriptions is also given to the participants to encourage them to undergo additional medical examination. The test results will be delivered by mail within two weeks after the analysis. In addition, HCV-positive patients who have not visited the hospital within a few months who receive a health check-up will be encouraged by the town to see a doctor. Such patients who regularly visit Yodakubo Hospital will be recommended by the doctor in charge to see a liver specialist. If the HCVAb test is positive, the participant will be recommended to consult a doctor in consideration of M2BPGi values, at which time serum HCV RNA measurement by the real-time polymerase chain reaction will be performed by an attending physician. If the participant is HCV RNA-positive, he or she will be referred to a hepatologist for further evaluation, whereby a definitive diagnosis of chronic hepatitis C will be ascertained according to diagnostic criteria by the Japan Society of Hepatology [13]. In such cases, DAA treatment will be initiated with patient consent by a hepatologist based on the guidelines of the Japan Society of Hepatology [13]. Patients will be monitored for a SVR every six months to calculate the SVR achievement rate in Nagawa town. Ultimately, the final HCV eradication rate will be determined on March 31, 2024.

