#### Study endpoints

The first endpoint in this study is determination of the prevalence of chronic hepatitis C patients in Nagawa town. The second endpoint is the rate of HCV elimination in Nagawa town on March 31, 2024.

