#### Statistical analysis

The HCVAb-positive rate and the HCV RNA-positive rate will be examined. In gender and age comparisons, continuous variables will be statistically evaluated by means of the Mann–Whitney U test, while categorical variables will be analyzed using the chi-square test in order to detect background differences. The HCV elimination rate will be examined at the end of the study.

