
Another possibility is that even if individuals know of their HCV infection, some avoid further consultation and DAA treatment in the absence of symptoms. Of the 1028 people in Nagawa town who underwent health check-ups in 2018, 139 (14%) received the HCVAb test. Three people were HCVAb-positive, among whom only two were recorded as having a secondary evaluation and had already been achieved an SVR by prior antiviral treatment. In order to motivate patients to action, the present study includes M2BPGi measurements to help visualize liver fibrosis stage. M2BPGi is low in healthy individuals and becomes significantly elevated with increasing liver fibrosis, and furthermore is associated with the development of HCC, liver-related complications, and prognosis [15–17]. Therefore, M2BPGi may be useful both as a first-line screening method in health check-ups as well as a motivational tool for suspected patients to undergo secondary screening. In order to achieve HCV eradication nationwide in Japan, more effective tactics will be needed.

Lastly, public awareness campaigns to share information on HCV will be important to maximize the examination and consultation rates. If the examination rate is too low, further information will be provided via the "Koho Nagawa" town publication and on Nagawa town cable television with the assistance of the Nagawa town government. In addition, we will promote the tests conducted in the Nagawa Project via hepatitis medical coordinators in the community. Residents who visit Yodakubo Hospital will also be given information via the hospital’s public relations magazine "Yodakubo Hospital Dayori".

Based on the above mentioned, it is highly likely that micro-elimination in the community can be achieved if this protocol is followed. For the residents of Nagawa town, the HCV test will enable earlier detection and initiation of eradication therapy, which will increase healthy life expectancy. As a downstream effect, this will also contribute to a reduction in future medical costs. In addition, once HCV micro-elimination in Nagawa town is declared, it will create a roadmap and greater opportunity for eliminating HCV in other parts of Nagano Prefecture and across Japan, with the goal of HCV elimination nationwide.

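### The town elimination rate has no numerator, denominator or success level, and the one outcome calculation described, an SVR rate in monitored patients, would not measure it

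*Protocol article*

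**What the plan says.** Study endpoints (Protocol article): "The second endpoint is the rate of HCV elimination in Nagawa town on March 31, 2024". Statistical analysis adds only that "The HCV elimination rate will be examined at the end of the study".

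Trial design and follow-up contains the one outcome calculation: "Patients will be monitored for a SVR every six months to calculate the SVR achievement rate in Nagawa town". The next sentence reads "Ultimately, the final HCV eradication rate will be determined on March 31, 2024". The third goal at the end of the Introduction names DAA treatment and the eradication rate together; screening and consultation are separate goals.

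The Introduction describes micro-elimination as working "by applying national-level eradication goals to specific populations, such as certain regions or people with certain demographics" and puts no figure on those goals. The Discussion nevertheless looks ahead to what follows "once HCV micro-elimination in Nagawa town is declared", and holds that "it is highly likely that micro-elimination in the community can be achieved if this protocol is followed".

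**The concern.** Three terms (SVR achievement rate, eradication rate, elimination rate) appear without being distinguished, and only the first is linked to any measurement. An SVR rate in monitored patients describes people who were tested, had RNA confirmed, consented to treatment and were followed. The Introduction already expects that figure to exceed 95%. It carries no information on infected residents who left the pathway earlier, and those residents decide whether the town is free of HCV.

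The plan leaves room for such losses. Non-consenters and some residents needing nursing care are outside the cohort (Inclusion and exclusion criteria). Consultation is recommended and treatment needs consent (Trial design and follow-up). Registration closes on September 30, 2023, six months before the endpoint date, so late cases may have no SVR result by then.

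Two things are at stake. A drug cure rate could be reported as town elimination. And because no level is fixed, whether micro-elimination has been reached could be decided after the results are seen.

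**Working it through.** **1. The plan's own figure.** Sample size estimation gives about 4500 adults and a positive rate of 0.35%: 4500 × 0.0035 = 15.75, or about 16. This reproduces. It is an expected count of HCVAb-positive residents, so on the protocol's own estimate it is a ceiling for the number viraemic.

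**2. What is defined.**

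| Term | Where | Numerator and denominator | Level for success |
|---|---|---|---|
| SVR achievement rate | Trial design and follow-up | not stated; patients monitored for SVR | none |
| Eradication rate | Trial design and follow-up; Introduction, goal 3 | not stated | none |
| Elimination rate | Study endpoints; Statistical analysis | not stated | none |

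**3. How far the candidate rates can differ.** Let s be the share of infected adults tested, l the share of HCVAb-positives who go on to RNA testing, t the share of RNA-positives treated, and c the SVR rate. Take c = 0.95, the lower edge of the Introduction's figure. The values of s, l and t are assumptions, and multiplying them assumes that infection status is unrelated to being tested or linked.

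- SVR among treated = c
- SVR among identified RNA-positives = t × c
- Share of all infected adults cured = s × l × t × c

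| s | l | t | Among treated | Among identified RNA-positives | Among all infected adults |
|---|---|---|---|---|---|
| 100% | 100% | 100% | 95% | 95% | 95% |
| 100% | 80% | 100% | 95% | 95% | 76% |
| 90% | 80% | 100% | 95% | 95% | 0.90 × 0.80 × 0.95 = 68% |
| 90% | 80% | 90% | 95% | 85.5% | 0.90 × 0.80 × 0.90 × 0.95 = 62% |
| 70% | 67% | 100% | 95% | 95% | 0.70 × 2/3 × 0.95 = 44% |

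The first rate never moves. The second moves only when diagnosed patients go untreated. RNA is measured at consultation, so untested and unconsulted residents never enter that denominator.

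**4. The same in residents.** Assume 8 to 16 viraemic adults (16 is the ceiling from step 1; 8 is an assumption). With t = 100%, the number still infected is:

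- 90% tested, 80% linked: 8 × (1 − 0.684) = 2.5 to 16 × (1 − 0.684) = 5.1
- 70% tested, 67% linked: 8 × (1 − 0.443) = 4.5 to 16 × (1 − 0.443) = 8.9

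At 0.35%, 10% untested adults (450) would hold about 450 × 0.0035 = 1.6 HCVAb-positive residents, and 30% untested (1350) about 4.7.

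**5. Precision.** When all n patients reach SVR, the exact 95% lower limit is 0.025^(1/n). For 8 of 8 it is 63%, and for 16 of 16 it is 79%. Even a perfect result is compatible with a much lower underlying rate.

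**The case against.** The strongest reply is that nothing in the article equates the elimination rate with the SVR rate. They are named in separate sentences, only the elimination rate is an endpoint, and a condensed article may leave the formula to a fuller document. This stands in part. A reader might infer that the plan has wrongly defined elimination as SVR among treated patients, and the text does not say so. The link is an inference from the adjacent sentences and from goal 3. What remains is that a named endpoint, and the project's ultimate aim, have no stated meaning, while the one calculation described would not measure them. Interval methods and the handling of losses could be left to an analysis plan. What the endpoint measures should not be.

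Second, coverage is not ignored. The Discussion aims at 100% testing, the town can identify every resident, and complete screening is a goal of its own. This is fair: the number untested should be knowable. But no coverage or linkage figure is tied to the endpoint or to the declaration.

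Third, the 2018 check-up data in the Discussion might tempt a reader to treat two of three as the expected linkage rate, or to see those two people as an example of a flattering SVR rate. Neither holds. Both had been cured by earlier treatment, so they would not be treated or monitored for SVR in this study. The count is three people, and the data predate the project's outreach. The 67% used above is therefore an assumption.

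Fourth, the declaration and the optimism about success are Discussion prose, not decision rules. A reader might infer that the optimism is shown to be wrong. It is not: without a stated level it can be neither supported nor refuted. The declaration is nonetheless the result that other regions are meant to build on.

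**Conclusion.** The point holds as a gap in the definition of the second endpoint. No numerator, denominator or success level is stated, and the SVR rate in monitored patients, if it were used, would omit residents lost before treatment or outside the cohort. The possible gap is large: 95% against 68% or 44% in the two main illustrations. Those figures rest on assumed tested and linked shares, full treatment of diagnosed patients, independence of the steps and SVR of exactly 95%. They show how the rates can diverge and do not predict the study's result. With full testing, linkage and treatment the gap vanishes. All viraemic counts are assumptions.

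**What to change.** 1. Define the elimination rate as eligible residents with SVR documented during the study, divided by all eligible residents found RNA-positive. Count untreated, declined, lost and SVR-pending residents at March 31, 2024 as not eliminated. Leave people cured before the study out of both parts. List deaths and move-outs separately.
2. Give an exact binomial interval. Report SVR among treated patients as supportive only.
3. Because this denominator cannot see unidentified infections, report beside it the tested share of the roughly 4500 adults, the RNA-tested share of HCVAb-positives, and an estimate of remaining viraemic residents. The estimate would add identified RNA-positives without SVR, unverified HCVAb-positives times an assumed viraemic share, and untested adults times an assumed viraemic prevalence, with the assumptions and their range shown.
4. Before analysis, fix the level of these quantities at which micro-elimination will be declared, and use one term for the endpoint throughout.

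The cost is mainly wording. Most of the data should arise from the planned testing and care pathway, but deaths and move-outs need some added record-keeping and the viraemic share has to be assumed. The headline rate may look less favourable.

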#### Study endpoints

The first endpoint in this study is determination of the prevalence of chronic hepatitis C patients in Nagawa town. The second endpoint is the rate of HCV elimination in Nagawa town on March 31, 2024.

#### Safety

In the Nagawa Project, blood samples will be collected during medical check-ups, with no additional intervention or invasiveness. Moreover, this study will be conducted free of charge and thus pose virtually no financial burden on the subjects. Therefore, the risk of non-participation is considered to be very low.

### Statistical considerations

#### Sample size estimation

We plan to screen all adult residents in the town of Nagawa (approximately 4500). Since the HCV-positive rate is reportedly 0.35% among workers in Japan [14], it is estimated that approximately 16 people are HCVAb-positive.

#### Statistical analysis

The HCVAb-positive rate and the HCV RNA-positive rate will be examined. In gender and age comparisons, continuous variables will be statistically evaluated by means of the Mann–Whitney U test, while categorical variables will be analyzed using the chi-square test in order to detect background differences. The HCV elimination rate will be examined at the end of the study.

## Discussion

The Nagawa Project is a prospective observational study that will screen all eligible residents for HCV infection and ultimately aims to achieve HCV micro-elimination in the town of Nagawa.

In spite of dramatic advances in DAA treatment for HCV, HCV micro-elimination has yet to be attained in any area of Japan. One possible reason is an unawareness of infection due to the asymptomatic nature of the liver until considerable disease progression, indicating that an HCVAb test is essential to learn of HCV infection. Therefore, in order to achieve micro-elimination, it is essential to establish a system in which all local residents can receive HCV testing. Nagawa town has been actively promoting health check-up services for decades and has established a system that allows residents to receive routine examinations at Yodakubo Hospital. In addition, many residents with chronic diseases visit the hospital on a regular basis. We examined the percentage of Nagawa town residents who had a health check-up or outpatient visit in 2019. Among patients using national health insurance and among the very elderly, the majority had the opportunity for a medical check-up or an outpatient blood test. In the remaining younger cases and residents using employee’s health insurance provided by the Social Health Insurance Unions and the Health Insurance Association of Japan (i.e.: Kyokai Kenpo), at least 46% had a medical check-up at Yodakubo Hospital for a chronic disease, although some residents underwent medical check-ups at other facilities. In our protocol, the township will identify all the residents, and they will be able to receive the test free of charge at their regular medical institutions. For those who do not have regular visits to the hospital, all residents will be given the opportunity to be tested by issuing a request form. Moreover, we offer preannounced days for free blood sample collection at Yodakubo Hospital for this minor population to attain 100% HCVAb testing. In addition, depending on the results, DAA treatment is also available. In order to increase a participating rate of 100%, this study is cooperated with the government of Nagawa town as well as Yodakubo hospital. Nagawa town can identify all its residents by their resident cards and town insurance cards. The insurance card makes it possible to ascertain whether a person has visited a hospital or had an examination. By issuing documents confirming that the residents have been inspected, it is possible to inform residents who have not been inspected and allow those who wish to be inspected to do so. In this way, all adults can be tested.

Another possibility is that even if individuals know of their HCV infection, some avoid further consultation and DAA treatment in the absence of symptoms. Of the 1028 people in Nagawa town who underwent health check-ups in 2018, 139 (14%) received the HCVAb test. Three people were HCVAb-positive, among whom only two were recorded as having a secondary evaluation and had already been achieved an SVR by prior antiviral treatment. In order to motivate patients to action, the present study includes M2BPGi measurements to help visualize liver fibrosis stage. M2BPGi is low in healthy individuals and becomes significantly elevated with increasing liver fibrosis, and furthermore is associated with the development of HCC, liver-related complications, and prognosis [15–17]. Therefore, M2BPGi may be useful both as a first-line screening method in health check-ups as well as a motivational tool for suspected patients to undergo secondary screening. In order to achieve HCV eradication nationwide in Japan, more effective tactics will be needed.

Lastly, public awareness campaigns to share information on HCV will be important to maximize the examination and consultation rates. If the examination rate is too low, further information will be provided via the "Koho Nagawa" town publication and on Nagawa town cable television with the assistance of the Nagawa town government. In addition, we will promote the tests conducted in the Nagawa Project via hepatitis medical coordinators in the community. Residents who visit Yodakubo Hospital will also be given information via the hospital’s public relations magazine "Yodakubo Hospital Dayori".

Based on the above mentioned, it is highly likely that micro-elimination in the community can be achieved if this protocol is followed. For the residents of Nagawa town, the HCV test will enable earlier detection and initiation of eradication therapy, which will increase healthy life expectancy. As a downstream effect, this will also contribute to a reduction in future medical costs. In addition, once HCV micro-elimination in Nagawa town is declared, it will create a roadmap and greater opportunity for eliminating HCV in other parts of Nagano Prefecture and across Japan, with the goal of HCV elimination nationwide.

